**Table 3 Tab3:**
[figure not shown]
Measurement periods (shaded cells) of the RE-AIM dimensions

Abbreviations: *C*  Cluster, *Q*  quarter of a year, *M*  month, *R*  Reach. *E*  Efficacy, *A*  Adoption, *I*  Implementation, *M*  Maintenance

### Intervention integrity

The integrity of the intervention will be measured during implementation and will be derived from the ‘Reach’, ‘Adoption’ and ‘Implementation’ dimensions of the RE-AIM framework, as can be seen in Table 3. As the integrity of the implementation of the four individual SUPREMOCOL pillars may not equally contribute to the successful implementation of the intervention in total, weight distribution between the four pillars will be applied. The weighing of these four items in the total intervention integrity degree will be determined by the participating SMHI’s and their chain partners of SUPREMOCOL. For this, the study methods for the weighting of fidelity items by stakeholders’ ratings by Oxman and colleagues [46] will be followed. The chain partners will be asked in a meeting to independently rate the relative importance of the variables belonging to the four pillars in successful implementation, by giving a score from 1 to 10 to the four pillars. Mean intervention degree ratings will be calculated, taking into account the weighing of these items.

#### Sample size

The sample size calculation is based on completed suicide rates, as this is the primary outcome of this study. The USA study of which we adapted our systems approach established a drop in potentially salvageable deaths from 34% (20/58) to 15% (9/60) (*p* < .02) following implementation, which is a Hazard Ratio of 2.3. We assume that in trauma patients, compliance of patients with entrance to care, if provided, was 100%, as the trauma is a one-time occurrence and involuntary. In people at risk for suicide, this risk may be sustained for a longer period of time, require multiple entrances into care and compliance may not always be the case. Hence, we want to be able to detect a smaller difference, which is of 20% in the completed suicides, as specified in our hypothesis. This corresponds to a rate ratio of 1.25. Based on an alpha of 0.05 (two-sided) and a power of 0.80, for this purpose, the minimal number of events would be 184 in each year. As completed suicides are the primary outcome we do not expect any loss to follow up for that outcome. As in 2017, the number of completed suicides in Noord-Brabant reported by Statistics Netherlands was 365, and all relevant settings in the region will collaborate, we expect that it will be feasible to find a difference of 20% in completed suicides, if such a difference exists, with an alpha of 0.05 and a power of 0.80.

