#### Statistical methods

To examine whether SUPREMOCOL leads to a reduction of completed suicides of 20% in the province of Noord-Brabant, the total number of completed suicides in the post-measurement will be compared to the total number of completed suicides in the pre-measurement. As the total number of residents in this province might have changed, we will also compare the pre- and post-incidence rates of suicides. An exact rate ratio test will be used. To take general trends over time into account, we will compare the incidence ratio in Noord-Brabant with the incidence ratios in other provinces in Noord-Brabant, and with the other provinces combined.

To examine whether SUPREMOCOL leads to a reduction of completed suicides and suicide attempts in association with the stepwise implementation of the system intervention in the subregions of the province, the total number of completed suicides and suicide attempts in each month will be compared to the two levels of our stepped wedge trial: region and time. A poison multilevel model will be used. The occurrence of completed suicide or admissions due to suicide risk in an SMHI will also be taken into account in the analysis. The suicide rates will be corrected for seasonal fluctuations [45]. In a second model, organisational differences between the regions, such as available number of crisis departments, will be taken into account. In a third model, the level of treatment integrity per subregion will be taken into account as well.

To explore whether SUPREMOCOL leads to a reduction of suicidal ideation in people registered in the monitoring system, the scores on the PHQ-9, SIDAS, and decision aid -that will be filled out by participants during the year that they receive the Supremocol additional care- will be compared by repeated measures. This will be used as exploratory process evaluation, as there is no control group for this.

To examine the impact of SUPREMOCOL with regards to reach, efficacy, adoption, implementation, and maintenance, an impact score will be calculated for each SMHI region and time period. This scores will be based on the function of all five RE-AIM dimensions, which are represented on a 0% (no impact) to 100% (best possible impact) scale [43].

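### The stated minimum of 184 suicides in each year does not give 80% power for the planned pre-post exact rate ratio test, which needs about 363 before and 290 after

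*Protocol article*

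**What the plan says.** The Sample size section of the protocol article sets out every input. The target is stated as "we want to be able to detect a smaller difference, which is of 20% in the completed suicides", and then: "This corresponds to a rate ratio of 1.25". The error rates follow: "Based on an alpha of 0.05 (two-sided) and a power of 0.80". The result is that "for this purpose, the minimal number of events would be 184 in each year". No formula or software is named. For this outcome "we do not expect any loss to follow up for that outcome". Feasibility is then argued from the fact that in 2017 "the number of completed suicides in Noord-Brabant reported by Statistics Netherlands was 365".

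The analysis is described elsewhere. The section on the primary outcome defines a pre-measurement year before any subregion enters the roll-out and a post-measurement year after all have done so, each covering the whole province. Statistical methods compares the two totals, and also the incidence rates, and specifies: "An exact rate ratio test will be used". The Background gives an earlier provincial count of 293 for 2014.

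**The concern.** A rate ratio test on a pre-year and a post-year count is a two-sample comparison. Both counts are random, and the variance of the contrast is the sum of two Poisson variances. A 20% reduction usually needs several hundred events in each year at conventional error rates, so 184 looks low.

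This is the only sample size justification given for the primary outcome. Setting 365 available events beside a minimum of 184 suggests a comfortable surplus (365/184 = 1.98). If the minimum is wrong, that surplus does not exist. A reader who relies on 184 would also take a null result from a year with fewer suicides as well powered when it is not.

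**Working it through.** **Inputs.** Post/pre ratio 0.80 (pre/post 1.25), two-sided alpha 0.05 (z = 1.95996), power 0.80 (z = 0.84162), and counts of 365 for 2017, all from Sample size; 293 for 2014 from Background. Assumptions: Poisson counts and equal person-time in the two years.

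**Step 1: reproduce 184.** Treat the pre-year count μ₀ as known and test one Poisson count against it:

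μ₀ = (1.95996 + 0.84162 × √0.8)² / (1 − 0.8)² = 2.71273² / 0.04 = 183.97, which rounds up to 184.

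The one-sample exact Poisson test at μ₀ = 184 has power 0.803. Other one-sample forms do not match (log scale 157.6; square-root scale 176.1; null variance only 196.2).

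**Step 2: two-sample requirement by normal approximation.**

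- Log rate ratio: pre-year events = (1.95996 + 0.84162)² × (1 + 1/0.8) / (ln 0.8)² = 7.849 × 2.25 / 0.04979 = 354.7. Post-year events = 0.8 × 354.7 = 283.7.
- Difference of counts: 7.849 × 1.8 / 0.04 = 353.2 pre-year.
- Square-root scale: 352.1 pre-year.
- Conditional binomial, with p = 0.8/1.8: total 633.4, that is 351.9 pre-year and 281.5 post-year.

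Even one-sided two-sample versions need 277 to 279 pre-year events. None of these two-sample forms comes near 184.

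**Step 3: the exact test that the plan names.** Given the total n, the post-year count is Binomial(n, 0.5) under no effect and Binomial(n, 0.8/1.8) under a 20% reduction. Reject when twice the lower-tail probability is at most 0.05. Power is the rejection probability averaged over a Poisson total. The smallest pre-year count that reaches 0.80 is 363 (power 0.801), with 0.8 × 363 = 290 expected in the post-year. Against the stated figure, 363/184 = 1.97.

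**Step 4: power at particular counts.**

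| Expected pre / post | Reading | Exact | Normal approx. |
|---|---|---|---|
| 184 / 147 | 184 is the pre-year count | 0.50 | 0.52 |
| 204 / 164 | 184 is the yearly average | 0.55 | 0.57 |
| 230 / 184 | 184 is the post-year count, a floor for both years | 0.60 | 0.62 |
| 293 / 234 | 2014 level | 0.71 | 0.72 |
| 355 / 284 | log rate ratio requirement | 0.79 | 0.80 |
| 365 / 292 | 2017 level | 0.80 | 0.81 |

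**Step 5: sensitivity for the comparison with the other provinces combined.** The article gives no count for the other provinces. It puts the national figure at almost 2000 a year, so I assume N = 1,400 to 1,700 elsewhere, unchanged over time. The standard error of the log ratio of ratios is √(1/365 + 1/292 + 2/N).

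- N = 1,400: √0.007593 = 0.0871; 0.2231/0.0871 − 1.960 = 0.60; power 0.73.
- N = 1,700: √0.007341 = 0.0857; 0.2231/0.0857 − 1.960 = 0.64; power 0.74.

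**The case against.** The strongest reply is that the plan's working conclusion is right. It claims that a 20% difference can be detected with 80% power given 365 suicides, and the exact calculation at 365 gives 0.803. The outcome counts every suicide in the province over two fixed years. It is not a recruitment target, so nothing stops at 184. That stands, and it limits the consequence: a reader might infer that the pre-post comparison is underpowered as planned, and at the plan's own baseline it is not.

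Four other readings go further than the article supports:

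- **That the authors used a one-sample formula.** The match at 183.97 is close and no two-sample form tried comes near, but no formula is named. The origin is an inference, and the error does not depend on it.
- **That 184 in both years contradicts a 20% effect.** It can be read as a floor for each year, with at least 184 after and so at least 230 before. Power is then 0.60, which is still inadequate.
- **That the plan claims a twofold margin.** It only sets the two numbers side by side, so the margin is implied.
- **That the comparison with other provinces misses a promised 0.80.** The Sample size section assigns no power to that contrast, and the figure in Step 5 rests on an assumed count.

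The 2014 count is likewise a sensitivity case: the Background describes a rising provincial trend, and 2017 is the more recent year.

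**Conclusion.** The stated minimum is wrong for the named test on every reading of the sentence. With a 20% reduction, two-sided alpha 0.05 and Poisson counts in two years of equal exposure, the requirement is about 363 and 290 events, nearly twice what is stated. The power actually delivered at 184 is 0.50 to 0.60.

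Feasibility of the simple pre-post test at the 2017 level stands, but with a reserve of two events instead of 181. A pre-year at the 2014 level would bring power to about 0.71, and variation beyond Poisson would lower it further. The result concerns only this pre-post test; the article states no calculation for the stepped wedge model, so there is none to check.

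**What to change.** In the Sample size section, replace the minimum of 184 for each year with about 363 in the pre-year and 290 in the post-year for the exact test. If 355 and 284 are quoted instead, label them as the normal approximation, because exact power there is 0.792. Name the formula or software used.

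State that the 2017 count of 365 gives about 80% power for the simple pre-post test with no reserve, and that power would be about 0.71 at the 2014 count of 293. Optionally, add the power for the comparison with the other provinces combined as a sensitivity figure (about 0.73 to 0.74), with the assumed 1,400 to 1,700 suicides a year elsewhere stated.

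The cost is one rewritten paragraph and a less favourable margin. The design, data collection and analysis do not change.

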#### Inclusion criteria

People who are registered in the monitoring system will be invited to participate in a survey evaluating suicidal ideation by filling out the PHQ-9 and SIDAS questionnaires. Inclusion criteria for participation in this survey are that participants are 1) 18 years or older and 2) Dutch-speaking. They will be asked for written informed consent, as further discussed in paragraph ‘Ethics approval and consent to participate’.

#### Statistical methods

To examine whether SUPREMOCOL leads to a reduction of completed suicides of 20% in the province of Noord-Brabant, the total number of completed suicides in the post-measurement will be compared to the total number of completed suicides in the pre-measurement. As the total number of residents in this province might have changed, we will also compare the pre- and post-incidence rates of suicides. An exact rate ratio test will be used. To take general trends over time into account, we will compare the incidence ratio in Noord-Brabant with the incidence ratios in other provinces in Noord-Brabant, and with the other provinces combined.

To examine whether SUPREMOCOL leads to a reduction of completed suicides and suicide attempts in association with the stepwise implementation of the system intervention in the subregions of the province, the total number of completed suicides and suicide attempts in each month will be compared to the two levels of our stepped wedge trial: region and time. A poison multilevel model will be used. The occurrence of completed suicide or admissions due to suicide risk in an SMHI will also be taken into account in the analysis. The suicide rates will be corrected for seasonal fluctuations [45]. In a second model, organisational differences between the regions, such as available number of crisis departments, will be taken into account. In a third model, the level of treatment integrity per subregion will be taken into account as well.

To explore whether SUPREMOCOL leads to a reduction of suicidal ideation in people registered in the monitoring system, the scores on the PHQ-9, SIDAS, and decision aid -that will be filled out by participants during the year that they receive the Supremocol additional care- will be compared by repeated measures. This will be used as exploratory process evaluation, as there is no control group for this.

To examine the impact of SUPREMOCOL with regards to reach, efficacy, adoption, implementation, and maintenance, an impact score will be calculated for each SMHI region and time period. This scores will be based on the function of all five RE-AIM dimensions, which are represented on a 0% (no impact) to 100% (best possible impact) scale [43].

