## Background

Completed suicides and suicide attempts c physical and emotional harm on the individual. Significant others, the community, and even entire nations suffer the consequences of such tragic events [1, 2]. Annually, more than 800,000 suicides occur worldwide, of which over 56,000 were reported in the European Union (EU), and almost 2000 in the Netherlands [1, 3, 4]. Although suicide rates in the Netherlands were equal to the EU-average [3], they did show a sharp incline of 37% between 2007 and 2013 [4]. This might be related to the economic recession in 2008 and rigorous budget cuts in the mental health sector [5, 6]. Since 2013, the relative suicide rate in the Netherlands has been stable, without decreasing [4]. In Noord-Brabant, one of the twelve provinces of the Netherlands, this stabilization in the suicide rates did not take place, as the absolute number of suicide in this province increased by 64%. Remarkably, 30% of this 64% increase in completed suicides happened in the years after 2013 [4]. At the start of the grant application for this study in 2015, Noord-Brabant even ranked second nationally over the five previous years (2010–2014) and there were 293 suicides in 2014, which is 11,5 suicides per 100,000 residents [4]. This poses a problem in the Netherlands and more specifically a regional problem in Noord-Brabant.

An important issue in effective suicide prevention is that approximately two-thirds of suicide victims were not receiving mental health care [7, 8], while they were probably in need of it, as suicide occurs mostly in the context of mental disorders [1, 2]. This might be due to a lack of visibility of people at risk, as help-seeking behaviour for suicidality is low, possibly due to stigma and poor suicide literacy [9]. Moreover, transitions of and discharges from care are associated with an increased risk of suicide attempt or death [10, 11]. An exploration amongst stakeholders identified that a tentative explanation might be a lack of communication between health care providers of different institutions or lack of swift entry into specialist care due to logistical barriers and waiting lists.

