### Scientific evaluation

#### Hypotheses

It is hypothesized that SUPREMOCOL will lead to a reduction of completed suicides of 20% in the province of Noord-Brabant, both in time and compared to the other provinces. Moreover, it is hypothesized that SUPREMOCOL will lead to less completed suicides and suicide attempts, both in association with the stepwise implementation of the system intervention in the subregions of the province, and will diminish suicidal ideation in people registered in the monitoring system.

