### Primary outcome: completed suicides

The primary outcome of this study is completed suicides. In the Netherlands, the occurrence of completed suicide is registered by coroners in the ORION system. The records from the ORION system regarding Noord-Brabant will be obtained from the Regional Public Health Institutes (PHI [in Dutch: Gemeentelijke Gezondheidsdienst; GGD]): GGD Brabant-Zuidoost, GGD West-Brabant, and GGD Hart voor Brabant. The PHI’s report their records to Statistics Netherlands, who collect the records for the whole country and make corrections if needed. To evaluate whether SUPREMOCOL leads to a reduction of completed suicides of 20% in the province of Noord-Brabant (hypothesis 1), completed suicides will be assessed during a one-year pre-post measurement for the total population of the province of Noord-Brabant. The pre-measurement will take place in the year before any of the areas in Noord-Brabant have entered the roll-out period (thus: 1 year before the start of period 1 of the SWT; therefore including period 0 of the SWT), and the post-measurement will take place in the year after implementation in all areas (thus: after period 5 of the SWT). National records from Statistics Netherlands will also be used for the pre-post evaluation, as completed suicide rates will be compared in time (pre-post) and per region (Noord-Brabant versus other provinces in the Netherlands). As it is also hypothesized that SUPREMOCOL leads to a reduction of completed suicides and suicide attempts in association with the stepwise implementation of the system intervention in the subregions of the province (hypothesis 2), completed suicides will also be assessed during the stepped wedge trial in the subregions of Noord-Brabant. Regional PHI records will be used for the SWT evaluation. For this, the total number of completed suicides per month will be examined.

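### Hypothesis 1 rests on an exact Poisson comparison of one year before with one year after, in a province whose own counts move by the target effect between two pre-trial years

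*Protocol article*

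**What the plan says.** The Primary outcome section fixes the window for hypothesis 1: "completed suicides will be assessed during a one-year pre-post measurement for the total population of the province of Noord-Brabant". The pre-year is the year before the first area enters roll-out, and the post-year follows implementation in all areas. No calendar dates are given. Statistical methods fixes the comparison ("the total number of completed suicides in the post-measurement will be compared to the total number of completed suicides in the pre-measurement"), repeats it on incidence rates because the population may have changed, and names an exact rate ratio test.

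The Hypotheses section expects the 20% reduction "both in time and compared to the other provinces". To allow for general trends, Statistical methods sets the Noord-Brabant incidence ratio against those of other provinces and of the other provinces combined. A monthly multilevel Poisson model for the stepped wedge is assigned to hypothesis 2.

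On the level of the outcome, the Background reports a national rate stable since 2013 and adds: "In Noord-Brabant, one of the twelve provinces of the Netherlands, this stabilization in the suicide rates did not take place". It also says "there were 293 suicides in 2014". The Sample size section gives 365 for 2017. It plans "Based on an alpha of 0.05 (two-sided) and a power of 0.80", says of the 20% difference "This corresponds to a rate ratio of 1.25", and concludes that "the minimal number of events would be 184 in each year".

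**The concern.** An exact test of two Poisson counts treats each year's total as a draw around a fixed underlying rate, so that only a change in that rate can separate the years beyond chance. The Background describes a rate that was not fixed: it was moving in this province while the national rate was flat. With one year on each side, the test cannot tell an intervention effect from an ordinary change of level between two years.

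The 20% claim for the province depends on this comparison. If the pre-year is high for reasons unrelated to the trial, a fall back would be credited to the intervention. If the province's rise continues, a real effect would be masked. In both cases the stated p-value and interval would be too confident.

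**Working it through.** **Inputs.** From the article: 293 (2014, Background), 365 (2017, Sample size), target ratio 0.80, two-sided alpha 0.05, power 0.80, equal one-year periods, and almost 2,000 suicides a year nationally (Background). Assumed: 2017 stands in for the undated pre-year; the population is equal in both years; the other provinces together have 1,400 to 1,635 deaths a year (the upper end is 2,000 − 365); and the extra between-year CV takes the values shown below.

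**1. The plan's own figure.** 184 is reproduced if the pre-year is treated as known without error:

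n = (1.960 + 0.842 × √0.8)² / 0.2² = 183.97.

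For two observed years, the usual formula gives

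n = (1.960 + 0.842)² × (1 + 0.8) / 0.2² ≈ 353 pre-year events.

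By simulation of the exact test, 184 pre-year events give about 50% power, and 365 falling to 292 gives about 80%. The feasibility conclusion therefore stands at 365, but only if the variation is purely Poisson.

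**2. The planned test on the article's two counts.** 293/365 = 0.803, a fall of 19.7%. The exact conditional test (293 of 658 against one half) gives p = 0.0056, 95% CI 0.69 to 0.94. From a pre-year of 365, any post-year count of 312 or fewer (14.5% lower) is significant.

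**3. A change of level without an effect.** If the underlying level went from 365 back to 293, the test would be significant in about 79% of simulated trials, close to its power for a true 20% effect. A halfway return, to (365 + 293)/2 = 329, gives p = 0.18 if that count is observed.

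**4. Type I error with extra-Poisson variation.** Simulated exact test, mean 365 in both years, no effect:

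| Assumed extra CV | Two-sided error | Of which false reductions |
|---|---|---|
| 0% | 4.5% | 2.2% |
| 3% | 8% | 4% |
| 5% | 15% | 7% |
| 8% | 27% | 14% |
| 10% | 35% | 18% |

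A hand check agrees. The variance is inflated by 1 + 365 × CV², which is 1.91 at 5% and 4.65 at 10%. Then 2Φ(−1.96/√1.91) ≈ 16% and 2Φ(−1.96/√4.65) ≈ 36%.

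**5. Does the comparison with other provinces remove it?** Take 365 to 293 in Noord-Brabant and 1,400 to 1,635 deaths elsewhere:

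- others flat: ratio of ratios 0.80, p about 0.011;
- others down 3%: 0.83, p about 0.03;
- others down 5%: 0.845, p about 0.05.

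**6. Power of that comparison.** For a true 20% effect, SE = √(1/365 + 1/292 + 2/m), with m the deaths per year elsewhere. With m = 1,600, SE = 0.0861 and power = Φ(0.2231/0.0861 − 1.960) = 0.74. With m = 1,400 it is 0.73, and with m = 1,635 it is 0.74. These figures assume Poisson variance.

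**7. What a longer baseline does.** If the level had been flat at 365, 3 or 5 pre-years would give power of about 0.87 or 0.90 (m = 1,600). The article describes a rise, not a flat level. Interpolating linearly from 293 to 365 (24 a year), the 2015 to 2017 counts are 317, 341 and 365, mean 341. A fall to 292 then appears as 1 − 292/341 = 14%, with power about 0.57. Extending the line back to five years gives a mean of 317, an apparent fall of 8% and power about 0.22.

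**The case against.** The strongest reply is that the plan does not rest on the pre-post test alone. Hypothesis 1 also requires a reduction against the other provinces, which deals with any shared national movement. Completed suicides are analysed again by month and subregion in the stepped-wedge model, which can adjust for time. Both points are true. But the provincial comparison uses the same two years, so a swing confined to Noord-Brabant passes through it (step 5), and the stepped-wedge model answers hypothesis 2, not the 20% claim.

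Other parts of the reply stand and limit the point:

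- A reader might infer textbook regression to the mean, with the province picked at its peak. The documents do not support this. The Background ties the case for the province to the 2015 grant application and data for 2010 to 2014, so it was not selected on the 365. An unstable, rising baseline is the accurate description, and the bias can run either way.
- A reader might infer that the trial would pass by drifting back to its 2014 level. That needs 2017 to resemble the pre-year, which is not dated, and a nearly full return, which nothing in the article predicts.
- The two-sided error rates should not be read as rates of false success. About half are apparent increases, and they concern the pre-post test alone. The CVs have no source in the article.
- A shortfall from 0.80 to about 0.74 is modest.
- An article may leave the handling of dispersion to the analysis plan. Here, though, it already names a test that has no place for extra variation.

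**Conclusion.** The concern holds as a matter of what the article fixes: a two-year exact Poisson test for its headline claim, where its own figures show a ratio of 0.803 (p = 0.0056) between two years that both precede the trial's registration in April 2018. The error bars are too narrow if the rate varies between years at all. At assumed extra CVs of 5% and 10%, the two-sided error is about 15% and 35%, and false reductions about 7% and 18%. The controlled half of hypothesis 1 has power of about 0.73 to 0.74, whereas the stated 0.80 belongs to the pre-post test.

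The direction of any bias is not known. The use of 2017 is illustrative, and the CVs and the number of comparator deaths are assumptions. The Potential limitations section does not mention baseline instability. The analysis should be changed before the post-year counts are examined.

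**What to change.** Make Noord-Brabant versus the other provinces combined the confirmatory contrast for hypothesis 1. Estimate it in one model of routine Statistics Netherlands counts for all twelve provinces over several pre-years and the post-year, with a population offset, province and year effects, and a term for Noord-Brabant in the post-year. Estimate the dispersion from the province-years (quasi-Poisson or negative binomial).

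Prespecify how the Noord-Brabant pre-trend is handled, for example by reporting the estimate with and without a province-specific trend. Province and year effects do not remove such a trend, so an averaged baseline alone is not enough. State the calendar dates of the pre- and post-years. Keep the one-year exact test and the single-province comparisons as descriptive, and restate the power for the controlled contrast.

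The cost is a revised analysis section and some further years of routine national counts. Intervals will probably be wider. If the pre-years were rising, an averaged baseline dilutes the apparent effect (step 7), so the change should be justified by validity and not presented as a gain in power.
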